## 1.8 Schematic Diagram

[figure not shown]

**1.9 FLOWSHEET FOR SCT PARTICIPANTS IN PILOT PHASE OF STUDY (first 15 randomisations to SCT).**

| WEEK                                              | Screening
-4 to -2 | Randomisation
0 | 1, 2, 3
(Mon) f | 4 | 8 | 12  | 24  | 36  | 48 | Further follow-up             | End of study
visit |
|---------------------------------------------------|-----------------------|--------------------|-------------------------------|---|---|-----|-----|-----|----|-------------------------------|-----------------------|
| SCT arm                                    |                       |                    |                               |   |   |     |     |     |    |                               |                       |
| Signed informed consent                           | X                     | (confirm)          |                               |   |   |     |     |     |    |                               |                       |
| Clinical assessment a                  | X                     | X                  |                               | X | X | X   | X   | X   | X  | Every 12 weeks                | X                     |
| Tanner scales                                     |                       | X                  |                               |   |   |     | X   |     | X  | Every 24 weeks                | X                     |
| Lipodystrophy assessment                          |                       | X                  |                               |   |   |     | X   |     | X  | Every 48 weeks                | X                     |
| Local HIV-1 RNA viral load g           | X                     | X                  | X                             | X | X | X   | X   | X   | X  | Every 12 weeks                | X                     |
| T cell lymphocyte subsets
inc. RO/RA phenotype | X                     | X                  |                               | X | X | X   | X   | X   | X  | Every 12 weeks                | X                     |
| Biochemistry b                         | X                     | X                  |                               |   |   | (X) | (X) | (X) | X  | As per local practise         | X                     |
| Haematology c                          | X                     | X                  |                               |   |   | X   | X   | X   | X  | Every 12 weeks                | X                     |
| Lipids/glucose d                       |                       | X                  |                               |   |   |     | X   |     | X  | Every 48 weeks                | X                     |
| Pregnancy Test e                       | X                     |                    |                               |   |   |     | X   |     | X  | Every 24 weeks                | X                     |
| Plasma storage g                       | X                     | X                  | X                             | X | X | X   | X   | X   | X  | Every 12 weeks                | X                     |
| Cell storage g                         | X                     | X                  |                               | X |   | X   | X   |     | X  | Every 24 weeks                | X                     |
| Adherence questionnaire                           | X                     |                    |                               | X |   | X   | X   | X   | X  | Every 12 weeks                | X                     |
| Acceptability Questionnaire                       |                       | X                  |                               |   |   |     |     |     |    | If re-start continuous
ART | X                     |
| PedsQL TM Questionnaire                |                       | X                  |                               |   |   |     | X   |     | X  | Every 24 weeks                | X                     |

Notes: shaded boxes indicate visits where overnight fasting is required for blood lipids/glucose.

(X) – Indicates optional investigations.

*If insufficient blood is drawn, priorities are: local HIV-1 RNA, T cell subsets, plasma store, lipids/glucose, biochemistry, and haematology*

(a) Clinical assessment: including height & weight (adjust doses), presence of adverse events and change in HIV disease stage (including clinical lipodystrophy).

(b) Biochemistry: Creatinine, Bilirubin, ALT, AST, Alkaline Phosphatase and Albumin. Calcium and Phosphate at baseline and annually thereafter.

(c) Haematology: Hb, MCV, WBC, Lymphocytes, Neutrophils, Platelets

(d) Lipids/Glucose: Triglycerides, Cholesterol (Total, HDL, LDL, VLDL), Glucose. Overnight fasting required at randomisation and weeks 24 and 48 and then every 48 weeks.

(e) Pregnancy Test: either a blood or urine sample. This test will be performed for all females of childbearing potential at screening and weeks 24 and 48 (then every 24 weeks) and at other time-points if required. The initial pregnancy test must be done within 72 hours of enrolment and its results must be received before randomisation.

(f) Weeks 1,2,3 phlebotomy visits should be before recommencing ART on the Monday; sufficient blood should be sent to the virology laboratory for a repeat measurement of the same sample.

(g) 16ml total blood draw in EDTA for plasma and cell storage: 6.0ml in EDTA if plasma store only (see Manual of Operations for instructions for plasma and cell handling and storage).

## 1.10 FLOWSHEET FOR CT PARTICIPANTS IN PILOT PHASE OF STUDY (first 15 randomisations to continuous arm).

| WEEK                                              | Screening
-4 to -2 | Randomisation
0 | 1, 2, 3
f | 4 | 8 | 12  | 24  | 36  | 48 | Further follow-up     | End of study
visit |
|---------------------------------------------------|-----------------------|--------------------|--------------|---|---|-----|-----|-----|----|-----------------------|-----------------------|
| SCT arm                                    |                       |                    |              |   |   |     |     |     |    |                       |                       |
| Signed informed consent                           | X                     | (confirm)          |              |   |   |     |     |     |    |                       |                       |
| Clinical assessment a                  | X                     | X                  |              | X | X | X   | X   | X   | X  | Every 12 weeks        | X                     |
| Tanner scales                                     |                       | X                  |              |   |   |     | X   |     | X  | Every 24 weeks        | X                     |
| Lipodystrophy assessment                          |                       | X                  |              |   |   |     | X   |     | X  | Every 48 weeks        | X                     |
| Local HIV-1 RNA viral load g           | X                     | X                  | X            | X | X | X   | X   | X   | X  | Every 12 weeks        | X                     |
| T cell lymphocyte subsets
inc. RO/RA phenotype | X                     | X                  |              | X | X | X   | X   | X   | X  | Every 12 weeks        | X                     |
| Biochemistry b                         | X                     | X                  |              |   |   | (X) | (X) | (X) | X  | As per local practise | X                     |
| Haematology c                          | X                     | X                  |              |   |   | X   | X   | X   | X  | Every 12 weeks        | X                     |
| Lipids/glucose d                       |                       | X                  |              |   |   |     | X   |     | X  | Every 48 weeks        | X                     |
| Pregnancy Test e                       | X                     |                    |              |   |   |     | X   |     | X  | Every 24 weeks        | X                     |
| Plasma storage g                       | X                     | X                  | X            | X | X | X   | X   | X   | X  | Every 12 weeks        | X                     |
| Cell storage g                         | X                     | X                  |              | X |   | X   | X   |     | X  | Every 24 weeks        | X                     |
| Adherence questionnaire                           | X                     |                    |              | X |   | X   | X   | X   | X  | Every 12 weeks        | X                     |
| PedsQL™ Questionnaire                             |                       | X                  |              |   |   |     | X   |     | X  | Every 24 weeks        | X                     |

Notes: shaded boxes indicate visits where overnight fasting is required for blood lipids/glucose.

(X) – Indicates optional investigations.

If insufficient blood is drawn, priorities are: local HIV-1 RNA, T cell subsets, plasma store, lipids/glucose, biochemistry, and haematology

(a) Clinical assessment: including height & weight (adjust doses), presence of adverse events and change in HIV disease stage (including clinical lipodystrophy).

(b) Biochemistry: Creatinine, Bilirubin, ALT, AST, Alkaline Phosphatase and Albumin. Calcium and Phosphate at baseline and annually thereafter.

(c) Haematology: Hb, MCV, WBC, Lymphocytes, Neutrophils, Platelets

(d) Lipids/Glucose: Triglycerides, Cholesterol (Total, HDL, LDL, VLDL), Glucose. Overnight fasting required at randomisation and weeks 24 and 48 and then every 48 weeks.

(e) Pregnancy Test: either a blood or urine sample. This test will be performed for all females of childbearing potential at screening and weeks 24 and 48 (then every 24 weeks) and at other time-points if required. The initial pregnancy test must be done within 72 hours of enrolment and its results must be received before randomisation.

(f) Weeks 1,2,3 phlebotomy visits at any time during the week; sufficient blood should be sent to the virology laboratory for a repeat measurement of the same sample.

(g) 16ml total blood draw in EDTA for plasma and cell storage: 6.0ml in EDTA if plasma store only (see Manual of Operations for instructions for plasma and cell handling and storage).

**1.11 FLOWSHEET FOR MAIN PHASE OF STUDY: SCT arm (after pilot fully recruited)**

| WEEK                                              | Screening
-4 to -2 | Randomisation
0 | 4 | 12  | 24  | 36  | 48 | Further follow-up             | End of study visit |
|---------------------------------------------------|-----------------------|--------------------|---|-----|-----|-----|----|-------------------------------|--------------------|
| SCT arm                                    |                       |                    |   |     |     |     |    |                               |                    |
| Signed informed consent                           | X                     | (confirm)          |   |     |     |     |    |                               |                    |
| Clinical assessment a                  | X                     | X                  | X | X   | X   | X   | X  | Every 12 weeks                | X                  |
| Tanner scales                                     |                       | X                  |   |     | X   |     | X  | Every 24 weeks                | X                  |
| Lipodystrophy assessment                          |                       | X                  |   |     | X   |     | X  | Every 48 weeks                | X                  |
| Local HIV-1 RNA viral load                        | X                     |                    | X | X   | X   | X   | X  | Every 12 weeks                | X                  |
| T cell lymphocyte subsets
inc. RO/RA phenotype | X                     | X                  | X | X   | X   | X   | X  | Every 12 weeks                | X                  |
| Biochemistry b                         | X                     | X                  |   | (X) | (X) | (X) | X  | As per local practise         | X                  |
| Haematology c                          | X                     | X                  |   | X   | X   | X   | X  | Every 12 weeks                | X                  |
| Lipids/glucose d                       |                       | X                  |   |     | X   |     | X  | Every 48 weeks                | X                  |
| Pregnancy Test e                       | X                     |                    |   |     | X   |     | X  | Every 24 weeks                | X                  |
| Plasma storage f                       | X                     | X                  | X | X   | X   | X   | X  | Every 12 weeks                | X                  |
| Cell storage f                         | X                     | X                  | X | X   | X   |     | X  | Every 24 weeks                | X                  |
| Adherence questionnaire                           | X                     |                    | X | X   | X   | X   | X  | Every 12 weeks                | X                  |
| Acceptability Questionnaire                       |                       | X                  |   |     |     |     |    | If re-start continuous
ART | X                  |
| PedsQL™ Questionnaire                             |                       | X                  |   |     | X   |     | X  | Every 24 weeks                | X                  |

Notes: shaded boxes indicate visits where overnight fasting is required for blood lipids/glucose.

(X) – Indicates optional investigations.

*If insufficient blood is drawn, priorities are: local HIV-1 RNA, T cell subsets, plasma store, lipids/glucose, biochemistry, haematology*

(a) Clinical assessment: including height & weight (adjust doses), presence of adverse events and change in HIV disease stage (including clinical lipodystrophy).

(b) Biochemistry: Creatinine, Bilirubin, ALT, AST, Alkaline Phosphatase and Albumin. Calcium and Phosphate at baseline and annually thereafter.

(c) Haematology: Hb, MCV, WBC, Lymphocytes, Neutrophils, Platelets

(d) Lipids/Glucose: Triglycerides, Cholesterol (Total, HDL, LDL, VLDL), Glucose. Overnight fasting required at randomisation and weeks 24 and 48 and then every 48 weeks.

(e) Pregnancy Test: either a blood or urine sample. This test will be performed for all females of childbearing potential at screening and weeks 24 and 48 (then every 24 weeks) and at other time-points if required. The initial pregnancy test must be done within 72 hours of enrolment and its results must be received before randomisation.

(f) 16ml total blood draw for plasma and cell storage: 6.0ml in EDTA if plasma store only. [see Manual of Operations for instructions for plasma and cell handling and storage].

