## 2.6 Risks and benefits

The potential risks of the SCT strategy are:

- The main risk is that the SCT strategy will prove ineffective in maintaining viral suppression, either because viral load cannot be maintained below detection levels during 2 days off ART, or due to non-adherence to the strategy by extending the time off treatment. However, if a raised viral load is confirmed on repeat testing (to be done within 1 week) then the participant will be placed back on continuous therapy.
- An additional risk is that young people, who have been fully adherent to ART prior to enrolment in the study, might extend the permitted very short interruptions and that overall adherence could decline. Of note, there is equipoise about whether adherence would be better or worse in the SCT arm compared with the continuous therapy arm as young people in the continuous arm may also not take their treatment regularly. All young people will be given diaries to record when they have taken ART and will be asked to comment about difficulties in remembering to take medication.  
Rebounding viral load comes with the risk of development of resistance (particularly to EFV and 3TC which have low genetic barriers to resistance) and which in turn may limit future therapeutic options. Resistance testing will be performed on all young people who lose virological suppression in either arm at the point of loss of suppression ( $\geq 50$  c/ml), as well as on any subsequent samples with HIV-1 RNA  $\geq 1000$  copies/ml.

The potential benefits of the SCT strategy are:

- Improvement in quality of life by having weekends free from taking medication.
- Improved long-term adherence during the week.
- Decreased long-term toxicity to antiretroviral drugs (particularly relevant for some NRTI drugs e.g. ZDV and TDF).
- Decreased cost which is important to any healthcare service, and in particular for many parts of the world where HIV prevalence is highest.

Young people and carers will be fully informed of possible benefits and known risks by means of a patient information sheet as appropriate and this will be reinforced by discussions with the study research teams at the individual sites prior to enrolment.

Data from the pilot phase have been reviewed by the IDMC who identified no safety concerns and recommended that recruitment continue.

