## 2. Short-Cycle Therapy (SCT)

This is a strategy trial. Blinding of patients to the randomised strategy would not be feasible and would be inappropriate as a key objective is to improve quality of life and adherence during the week by allowing days off at the weekend.

Recruitment of a minimum of 160 young people will be over a total of 27 months. All participants will be followed until the last participant has completed 48 weeks of follow-up. Young people and/or caregivers will be asked to consent to routine clinical data being provided for two years after the main trial is complete. Further information on long term follow can be found in Section 8.10.

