### **Secondary Outcomes:**

The efficacy and safety of SCT and continuous ART will also be compared through the analysis of HIV-1 viral load and T cell subsets measured locally at each protocol visit, the presence of mutations conferring resistance to drugs taken at randomisation or during the trial, changes in the stage of a young person's HIV disease (CDC classification – see Appendix 8) measured at trial entry and each protocol visit, and the presence of adverse events. To assess the advantages and disadvantages of the strategy, acceptability, quality of life and adherence to the randomised strategy will also be compared. Specifically, the secondary outcomes of the trial are:

- HIV-1 RNA  $< 50$  c/ml at 24 and 48 weeks.
- Number of HIV mutations present at week 4, 12, 24, 36 or 48 conferring resistance to drugs taken at randomisation or during the trial
- Change in CD4 (absolute and percentage) from randomisation to 24 and 48 weeks
- Change in ART (defined as any change from the ART regimen at randomisation)
- Grade 3 or 4 clinical and laboratory adverse events.
- ART treatment modifying adverse events (all grades).
- New CDC stage B or C diagnosis or death
- Changes in fasting glucose, cholesterol, triglycerides, LDL, HDL and VLDL levels through 48 weeks
- Adherence, acceptability, and quality of life over 48 weeks as assessed by patient completed questionnaires
- HIV-1 RNA  $\geq 50$  c/ml (confirmed on a separate sample within 1 week) at any time throughout follow up
- HIV-1 RNA  $< 50$  c/ml at 96 and 144 weeks.
- Adherence over the duration of the trial, as assessed by patient completed questionnaires.
- Change in CD4 (absolute and percentage) from randomisation to 96 and 144 weeks.
- 

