## **11.6 Analysis plan**

Intention-to-treat analyses will be performed on all randomised participants. Statistical methods include:

- Descriptive statistics for the summary of baseline characteristics
- Fishers exact test and logistic regression models for the analysis of binary outcome variables
- Analysis of variance and linear regression models for the analysis of continuous outcome variables, adjusting for baseline
- Poisson regression for the analysis of the incidence rate of clinical/adverse events
- Log rank test and proportional hazards regression models for the analysis of time to event variables

The incidence rate of clinical/adverse events will be summarised by body system and randomised arm. First events (in terms of time to first event) and all events will be considered.

Major resistance mutations will be defined by the current IAS-USA list.

The primary outcome for the main study is HIV-1 RNA  $\geq 50$  c/ml (confirmed on a separate sample within 1 week) at any of week 4, 12, 24, 36 or 48. This outcome only considers HIV-1 RNA measurements at these time points due to the difference in viral load monitoring in the pilot phase and the main trial. However if a young person enrolled in the pilot phase has an HIV-1 RNA  $\geq 50$  copies/ml at weeks 1, 2 or 3 (reproducible on the same sample) or at week 8 (confirmed on a separate sample within 1 week) they will be considered as reaching the primary outcome at week 4 and 12 respectively. All participants will be analysed in the arm to which they were randomised (intention to treat).

A full Statistical Analysis Plan (SAP) will be developed as a separate document.

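### Most biochemistry panels between baseline and week 48 are discretionary in an open-label trial, so the biochemistry part of the grade 3/4 laboratory comparison is open to unequal ascertainment

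*Combined protocol and SAP*

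**What the plan says.** All four main-trial flowsheets (sections 1.9 to 1.12, pilot and main phase, both arms) give biochemistry the same schedule. It is required at screening, week 0, week 48 and the end of study visit. At weeks 12, 24 and 36 it carries a bracketed mark, explained under each table as "Indicates optional investigations". In further follow-up the entry is "As per local practise". No criterion is given for when an optional panel should be done. The panel covers the transaminases, alkaline phosphatase, bilirubin, creatinine and albumin; calcium and phosphate have their own annual timing.

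Other laboratory safety tests are fixed. Haematology is required at weeks 12, 24, 36 and 48 and 12-weekly after that. Lipids and glucose are required at weeks 24 and 48 and then every 48 weeks.

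The secondary outcomes in sections 1.4, 4.2 and 11.2 include "Grade 3 or 4 clinical and laboratory adverse events". Section 2.6 lists less long-term drug toxicity among the potential benefits of short-cycle therapy (SCT). Section 4.1 says of masking that "Blinding of patients to the randomised strategy would not be feasible". Section 11.6 names "Poisson regression for the analysis of the incidence rate of clinical/adverse events", considers both first events and all events, and defers detail to a separate statistical analysis plan.

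**The concern.** A laboratory event can be counted only if someone takes the sample. Where three of four panels to week 48 are at the clinician's discretion, and the clinician knows the allocation, the two arms may be sampled at different rates. A clinician might order more panels in participants on the untested strategy, or fewer because drug exposure is lower. The direction cannot be predicted.

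The protocol also contains a structural route to unequal testing. Under section 7.5.2, SCT participants who return to continuous therapy after rebound are seen at 4 and 12 weeks and then 12-weekly, on flowsheet 1.12. Where that adds visits, it adds occasions for optional panels in the SCT arm only. Section 8.1 further allows extra visits in either arm at the clinician's request.

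Nothing in section 11.6 guards against this. A rate per unit of follow-up time treats a participant with one panel and a participant with four as equally observed. The fault would be a difference in biochemical toxicity, in either direction, that reflects sampling and not drug effect, in a trial that sets out to compare toxicity between strategies. A transient creatinine or transaminase rise that resolves before week 48 is seen only if a panel happened to be ordered.

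**Working it through.** The plan states no figure on this point, so there is nothing to reproduce. The check counts scheduled tests and then illustrates what unequal testing could do.

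**Step 1: post-baseline tests to week 48, either arm (flowsheets 1.9 to 1.12).**

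| Test group | Required | Optional | Share discretionary |
|---|---|---|---|
| Biochemistry | 1 (week 48) | 3 (weeks 12, 24, 36) | 3/4 = 75% |
| Haematology | 4 | 0 | 0% |
| Lipids/glucose | 2 | 0 | 0% |

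**Step 2: illustration with no true difference.** Let p be the chance that one panel shows a grade 3/4 value, equal in both arms, and q the share of the three optional visits at which a panel is done. Both are assumptions, since the documents give neither. With independent panels, the chance of at least one recorded biochemical event to week 48 is

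1 - (1 - p)(1 - pq)^3.

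For p = 1%:
- q = 0.9: 1 - 0.99 x 0.991^3 = 3.65%. q = 0.6: 1 - 0.99 x 0.994^3 = 2.77%. Ratio 1.32.
- q = 0.8: 3.36%. q = 0.4: 2.18%. Ratio 1.54.
- q = 1: 3.94%. q = 0: 1.00%. Ratio 3.94.

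Varying p from 0.5% to 3%, the ratios run 1.31-1.32, 1.52-1.54 and 3.82-3.97. With equal q the ratio is 1.00 for any p.

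For a count of all events over equal follow-up, as a Poisson model would use, the spurious rate ratio is the ratio of expected panels and does not depend on p: (1 + 3 x 0.9)/(1 + 3 x 0.6) = 3.7/2.8 = 1.32, and (1 + 3 x 0.8)/(1 + 3 x 0.4) = 3.4/2.2 = 1.55.

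**Step 3: dilution by fixed tests.** Add four haematology tests at the same assumed p, giving 1 - (1 - p)^5 (1 - pq)^3. For p = 1% to 2% the ratios fall to 1.12-1.13 (90% v 60%), 1.18-1.19 (80% v 40%) and 1.55-1.58 (100% v 0%).

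**Step 4: chance of a nominally significant spurious difference in biochemistry.** Two-sided 5% test, 80 to 110 per arm (the 160 to 220 total in section 11.3), p from 1% to 3%, normal approximation: 5-9% at 90% v 60%, and 7-15% at 80% v 40%, against a nominal 5%. With so few expected events these are rough.

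**Step 5: effect of restricting to required panels.** Both arms then have the same scheduled panels, so with equal true rates and equal attendance the ratio is 1.00. The price is events. At p = 1% and 80 per arm, the week 48 and end of study panels give 80 x (1 - 0.99^2) = 80 x 1.99% = 1.6 participants with an event per arm. All four panels to week 48 plus the end of study panel would give 80 x (1 - 0.99^5) = 80 x 4.90% = 3.9.

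**The case against.** The strongest reply is that the rule is the same in both arms. Bias needs testing to differ by arm, and no passage shows that it did; equal under-testing loses events and precision but favours neither arm. That stands. The point is an unguarded exposure, not a demonstrated bias.

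The schedule was also a deliberate choice: the amendment record in section 18 shows biochemistry being moved to local practice. Participants are stable on first-line treatment, those with grade 3 or higher creatinine, AST or ALT at screening are excluded, adverse events are recorded at every visit, and investigators must see participants as often as safety requires. This is a fair defence of lighter testing. It does not address how the arms are then compared. Nor was biochemistry regarded as unimportant: section 8.4 lists it for efficacy and safety monitoring, and the flowsheet notes rank it above haematology when blood is short.

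The full statistical analysis plan is a separate document whose text is not included here, and it may already contain a safeguard. Section 11.6 also names Fisher's exact test, logistic regression and time-to-event methods, so rates are not the only route. But none of these, as described, allows for the number of tests done.

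Finally, persistent abnormalities would be found at week 48 whatever the earlier testing, which pulls the ratios in the working towards 1. That is correct; the illustration suits transient events best.

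**Conclusion.** The point holds for one component: biochemical grade 3/4 events found between baseline and week 48, and between week 48 and the end of study visit. Their ascertainment is discretionary or local, allocation is open, and the analysis section does not allow for testing frequency. Plausible imbalances give spurious biochemistry risk ratios of about 1.3 to 1.5, less once fixed haematology is pooled in. These figures rest on assumed per-panel risks of 0.5-3%, assumed testing shares, and independence between panels.

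A reader might infer more than the documents support:

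- That the whole laboratory comparison depends on who chose to test. It does not: haematology and lipids/glucose are fixed in both arms, and biochemistry is required at week 48 and end of study.
- That a fourfold artefact is a realistic risk. A ratio near 4 needs every optional panel done in one arm and none in the other.
- That lower toxicity is a claim the trial was built to establish. Section 2.6 lists it only as a potential benefit, and the sample size rests on HIV-1 RNA suppression.
- That the data monitoring committee's tables would be distorted. Section 11.4 does not describe their content.

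The primary outcome is untouched. Severity is minor.

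**What to change.** Add the following to section 11.6, or to the separate analysis plan if it does not already say so:

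1. Keep every grade 3/4 event in the safety tables, whichever panel found it.
2. Report the number of biochemistry panels done per participant, by arm, to week 48 and after week 48.
3. Add a between-arm comparison of biochemical grade 3/4 events restricted to the required panels (week 48 and end of study), and rely on it if testing frequency differs by arm. Time these visits from randomisation, so that SCT participants moved to flowsheet 1.12 are handled in the same way as everyone else.

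The cost is one table and one extra analysis. The downside is fewer events and less precision in the restricted comparison (about 1.6 against 3.9 expected participants with an event per arm in the example above), which is why it should supplement the full listing and not replace it.

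Requiring panels at weeks 12, 24 and 36 would remove the problem at source, but it reverses a deliberate choice and adds tests. It also comes too late for this version of the protocol, dated May 2015: final follow-up visits are set for April to July 2016, two years after main-trial completion, which puts that completion at about April to July 2014.
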